## **8.0 SAFETY REPORTING**

### **8.1 Safety Assessments**

Safety assessments will be performed during screening, at baseline, at weeks 1, 2, 4, 6, 8, 12 and then every 6 weeks throughout the 48 weeks treatment period. Safety assessments will continue at weeks 50, 52, 56, 60 and 72 during the follow up period, as outlined in Section 4.1. Patients prematurely discontinued from test drug therapy will have a safety assessment 4 and 12 weeks after their last dose of study medication. Clinically significant laboratory abnormalities should prompt repeat measures no less frequently than every 4 weeks or in shorter intervals as clinically indicated, with appropriate clinical management, until values return to normal or baseline levels.

Measures of safety will include assessment of AEs, vital signs (systolic and diastolic blood pressure and pulse rate), and laboratory tests in addition to those carried out for efficacy as well as documentation of dose adjustments and premature withdrawals from treatment for safety or tolerability reasons. Patients with preexisting ophthalmologic disorders (e.g. diabetic or hypertensive retinopathy) should receive periodic ophthalmologic exams during therapy.

### **8.2 Section 10 WMO event**

In accordance to section 10, subsection 1, of the WMO, the investigator will inform the subjects and the reviewing accredited METC if anything occurs, on the basis of which it appears that the disadvantages of participation may be significantly greater than was foreseen in the research proposal. The study will be suspended pending further review by the accredited METC, except insofar as suspension would jeopardise the subjects' health. The investigator will take care that all subjects are kept informed.

### **8.3. Adverse and serious adverse events**

Adverse events are defined as any undesirable experience occurring to a subject during a clinical trial, whether or not considered related to the investigational drug.

A serious adverse event is any untoward medical occurrence or effect that at any dose results in death;

- is life threatening (at the time of the event);
- requires hospitalisation or prolongation of existing inpatients' hospitalisation;
- results in persistent or significant disability or incapacity;
- is a congenital anomaly or birth defect;

- is a new event of the trial likely to affect the safety of the subjects, such as an unexpected outcome of an adverse reaction, lack of efficacy of an IMP used for the treatment of a life threatening disease, major safety finding from a newly completed animal study, etc.

Medical and scientific judgment should be exercised in deciding whether expedited reporting is appropriate in other situations, such as important medical events that may not be immediately life-threatening or result in death or hospitalization but may jeopardize the patient or may require intervention to prevent one of the outcomes listed in the definitions above. These situations should also usually be considered serious.

The term severe is a measure of intensity, thus a severe adverse event is not necessarily serious. For example, nausea of several hours' duration may be rated as severe, but may not be clinically serious.

A death occurring during the study or which comes to the attention of the investigator within 4 weeks after stopping the treatment or during the 24 weeks of protocol-defined follow-up period, whether considered treatment-related or not, must be reported.

Any pregnancy which occurs during a clinical study with an investigational drug must be reported as an SAE for tracking purposes. All pregnancies which are identified during this study need to be followed to conclusion and outcome reported.

Female patients should immediately inform the Investigator of any pregnancies and should be instructed by the Investigator to stop taking study medication. (Pregnancies occurring up to 3 months after the completion of the study must also be reported to the Investigator). The Investigator should counsel the patient, discuss the risks of continuing with the pregnancy and the possible effects on the fetus. Monitoring of the patient should continue until the conclusion of the pregnancy.

Such preliminary reports will be followed by detailed descriptions later which will include copies of hospital case reports, autopsy reports and other documents when requested and applicable.

For serious and all other AEs, the following must be assessed and recorded on the AE page of the CRF: intensity, relationship to test substance, action taken regarding test substance, and outcome to date.

On the SAE form a drug/event relationship must be provided for each study medication (Yes or No) and each event. "Yes" must be entered for a causality of remote, possible, probable,

i.e., there is a reasonable suspected causal relationship, or causality is unknown. No is to be entered for a causality of not related.

The investigator will notify the Ethics Committee (METC) of such an event in writing in accordance with local laws and regulations. The investigator will notify the Health Authorities. The definitions for and procedures for reporting SAEs to Health Authorities will be taken from the ICH-GCP and the Dutch law 'Wet medisch-wetenschappelijk onderzoek met mensen' (WMO).

### **8.3.1. unsuspected unexpected serious adverse reactions (SUSAR)**

Adverse reactions are all untoward and unintended responses to an investigational product related to any dose administered.

Unexpected adverse reactions are adverse reactions, of which the nature, or severity, is not consistent with the applicable product information (e.g. Investigator's Brochure for an unapproved IMP or Summary of Product Characteristics (SPC) for an authorised medicinal product).

The investigator will report expedited the following SUSARs to the METC:

- SUSARs that have arisen in the clinical trial that was assessed by the METC;
- SUSARs that have arisen in other clinical trial of the same sponsor and with the same medicinal product, and that could have consequences for the safety of the subjects involved in the clinical trial that was assessed by the METC.

The remaining SUSARs are recorded in an overview list (line-listing) that will be submitted once every half year to the METC. This line-listing provides an overview of all SUSARs from the study medicine, accompanied by a brief report highlighting the main points of concern.

The sponsor will report expedited all SUSARs to the competent authority, the Medicine Evaluation Board and the competent authorities in other Member States.

The expedited reporting will occur not later than 15 days after the investigator has first knowledge of the adverse reactions. For fatal or life threatening cases the term will be maximal 7 days for a preliminary report with another 8 days for completion of the report.

### **8.3.2 Annual safety report**

In addition to the expedited reporting of SUSARs, the sponsor will submit, once a year throughout the clinical trial, a safety report to the accredited METC, competent authority, Medicine Evaluation Board and competent authorities of the concerned Member States.

This safety report consists of:

- a list of all suspected (unexpected or expected) serious adverse reactions, along with an aggregated summary table of all reported serious adverse reactions, ordered by organ system, per study;
- a report concerning the safety of the subjects, consisting of a complete safety analysis and an evaluation of the balance between the efficacy and the harmfulness of the medicine under investigation.

### **8.3.3. Pregnancy**

Pregnancy is to be strictly avoided during the course of this trial. However, if a female subject becomes pregnant during the study she must be instructed to stop taking the trial medication and immediately inform the investigator. Pregnancies occurring up to 12 weeks after the completion of the trial medication must also be reported to the investigator. The investigator should counsel the subject, discuss the risks of continuing with the pregnancy and the possible effects on the fetus. Monitoring of the patient should continue until conclusion of the pregnancy.

### **8.4 Follow-up of adverse events**

All adverse events will be followed until they have abated, or until a stable situation has been reached. Depending on the event, follow up may require additional tests or medical procedures as indicated, and/or referral to the general physician or a medical specialist.

## 9 STATISTICAL ANALYSIS

### 9.1 Descriptive statistics

The main efficacy variable in the comparison of treatments A and B to treatment C ( no treatment) is the proportion of subjects in each treatment group achieving loss of HBsAg. The primary objective is to demonstrate superior efficacy of treatment A and/or B to treatment C.

The sample sizes were calculated as follows:

Per treatment group 44 per group (88 for both groups) is needed to achieve 81% power to detect a difference between the two treatment groups and the control group. The proportion in the PEG/IFN and adefovir group is assumed to be 0.01 under the null hypothesis and 0.20 under the alternative hypothesis. The proportion in the control group (no treatment) is 0.01. The statistical test used is the two-sided Fisher's Exact test . The significance level of the test was targeted at 0.05. A group sample of 44 persons in the control group is needed to achieve a 81% power to detect a difference between the PEG/IFN adefovir or PEG/IFN tenofovir.

Regarding a 10% drop-out due to peginterferon side-effects or other reasons a total of 50 patients are needed in each group.

Univariate logistic regression analyses will be performed to identify predictors of response to the combination therapy of PEGASYS® and ADF dipivoxil (Hepsera®) and PEGASYS® and tenofovir. Significant predictors from the univariate analysis will be combined into a multivariate logistic regression analysis. As a rule of thumb, the number of potential predictors to be included in a multivariate analysis should not exceed the number of responders (or non-responders, whichever is the lowest) divided by 10. With 100 patients included, the maximum number of predictors in a multivariate analysis is five, assuming a response rate of 0.50. Initially, the number of significant predictors from univariate analysis to be included in the multivariate analysis will be restricted following multi colinearity diagnostics. If the number of potential predictors remains too large however, a bootstrap procedure will be followed drawing 200 samples of the same size as the original (n=100) with replacement, each time repeating the multivariate logistic regression analysis. Descriptives of this bootstrap procedure will be reported to identify a stable predictor set. The level of significance during all these analyses is set at 0.05.

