In our currently ongoing study in patients with a high viral load (HBV DNA  $\geq$  20,000 IU/mL) combination therapy of Peg-IFN and ADF, a rate of 23% HBsAg loss was reported after one year of therapy, which is much higher than currently is observed with other treatment regimens (6). Moreover in this study a positive predictive value of HBsAg loss of 85% was seen when baseline HBsAg levels were less than 675 IU/mL, suggesting that patients with lower baseline HBsAg levels are more susceptible to HBsAg clearance. Treatment in these patients was well tolerated, 4% developed thyroid disease which is comparable to other studies (31). Recent studies have shown that tenofovir is a more potent viral suppressor than adefovir (32). Moreover it has recently been reported that the rate of HBsAg loss in HBeAg positive patients after 2 years of tenofovir (TDF) therapy was 6% (33).

Chronic hepatitis B patients with low viral load (HBV DNA < 20,000 IU/mL) most often have inactive disease and don't require viral suppression according to Dutch guidelines (34). However in the light of the currently highly successful rate of HBsAg loss seen in our ongoing study (6) we hypothesize that a similar rate of HBsAg clearance can be achieved in HBeAg negative patients with low HBV DNA viral load, thereby focusing on cure of the disease rather than viral suppression.

In the light of the suboptimal therapies currently available e.g. the dose limiting adverse reactions of Peg-INF treatment and the development of drug resistance, it is of great practical value to establish predictors of response (or non-response) before or early in the course of anti-viral treatment to assess the success rate of antiviral agents and to guide therapeutic interventions in hepatitis B.

In this study we hypothesize that both treatment with peg-interferon and ADF or Peg-IFN and TDF in HBeAg negative chronic hepatitis B patients with low HBV DNA viral load will induce a high rate of HBsAg loss, comparable to that in patients with high viral load after treatment with ADF and Peg-IFN.

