### 2.2. Secondary Objective:

The secondary objectives are to evaluate:

- a. the rate of HBsAg loss and anti-HBs serconversion,
- b. To establish predictive markers at baseline and during the first 12 weeks of treatment for response of primary and secondary endpoints:

serologic markers

HBsAg levels

immunologic markers

T cell responses, cytokine production of T cells.

histologic markers

HAI (histology activity index)

Fibrosis grade

HBsAg level

cccDNA level (liver)

HBV-DNA level (liver)

biochemical markers (livertransaminases)

ALT

AST

LDH

AF

yGT

virologic markers

HBsAg level

cccDNA (plasma)

HBV-DNA level

HDV co-infections

Hostgenomics

DNA and RNA expression levels in PBMC's, liver

Proteomics

Possible protein candidates include: SR-B1(CD36), CD81, certain Claudins, STAT-1 and 2, ApoE and more

Inflammatory markers

CRP, neopterin

Neoplastic markers

Rate of development of hepatocellular carcinoma

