### **7.2. Randomisation, blinding and treatment allocation**

Patients will be randomized unblinded to one of the 3 groups. A stratification for hepatitis B genotype A will be performed.

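### Predictor screening in Section 9.1 pools both active arms without the randomised regimen, so a week 1–12 marker can be flagged for differing by regimen rather than for predicting HBsAg loss

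*Protocol*

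**What the plan says.** Section 9.1 states: "Univariate logistic regression analyses will be performed to identify predictors of response to the combination therapy of PEGASYS® and ADF dipivoxil". In full, the aim is to "identify predictors of response to the combination therapy of PEGASYS® and ADF dipivoxil (Hepsera®) and PEGASYS® and tenofovir". The method is univariate logistic regression. Markers significant at 0.05 go into a multivariable logistic model, with a bootstrap if too many remain.

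The analysis set is the two active arms combined: "With 100 patients included, the maximum number of predictors in a multivariate analysis is five, assuming a response rate of 0.50". The bootstrap repeats this, "drawing 200 samples of the same size as the original (n=100) with replacement". No regimen term is named at any step, and regimen is not in the list of candidate markers in Section 2.2.

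Objective 2.2b is "To establish predictive markers at baseline and during the first 12 weeks of treatment". The list includes HBV DNA, HBsAg level and transaminases, and Table 2 (Appendix) samples these repeatedly between baseline and week 12.

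On the two drugs, Section 1 says: "Recent studies have shown that tenofovir is a more potent viral suppressor than adefovir". For response, Sections 4.4 and 9.1 assume 0.20 in the adefovir arm and give no separate rate for tenofovir. Section 1 hypothesises a high rate of HBsAg loss with both regimens.

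**The concern.** A marker measured after randomisation can be affected by the drug received. If the two regimens shift the marker differently and also differ in HBsAg loss, regimen is a common cause of both. In the pooled data the marker is then associated with loss even if, among patients on the same regimen, it says nothing about who responds.

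The screening step cannot correct this, because a univariate model has room for the marker only. The multivariable step takes forward what passed the screen, and the bootstrap repeats that multivariable model on the same pooled set.

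Section 1 wants early predictors so that they can guide therapy. A marker that mainly separates the two regimens would be reported as a predictor of response without helping to judge any patient on a given regimen.

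**Working it through.** **The plan's own figure.** The predictor cap is the smaller of responders and non-responders, divided by 10. At a response rate of 0.50: 100 × 0.50 / 10 = 5, as stated. At the planned 0.20 the same rule gives 100 × 0.20 / 10 = 2. This bears on the cost of the fix.

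**Inputs.** From the protocol: 50 + 50 treated patients, test level 0.05, average response 0.20. Assumed, because the protocol gives neither: the difference in HBsAg loss between regimens, and the marker difference between regimens (*d*, in within-arm SDs). The marker is set to have no relation to loss within either regimen.

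**Why both differences are needed.** With equal arms, the pooled covariance of marker and response is *d* × Δ / 4, where Δ is the difference in loss. It is zero if either is zero. The pooled marker variance is 1 + *d*²/4, and the response variance is 0.20 × 0.80 = 0.16. For *d* = 1:

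- Δ = 0.10: r = 0.025 / √(1.25 × 0.16) = 0.056. Expected z = 0.056 × √100 = 0.56. Rejection ≈ Φ(−1.40) + Φ(−2.52) ≈ 0.087.
- Δ = 0.20: r = 0.112 and z = 1.12. Rejection ≈ Φ(−0.84) + Φ(−3.08) ≈ 0.20.

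**Simulation.** Logistic likelihood-ratio tests at 0.05, 2,000 trials per setting; false-positive rate for the marker:

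| HBsAg loss, arm 1 v arm 2 | *d* | No regimen term | Regimen term |
|---|---|---|---|
| 20% v 20% | 1 | 5.3% | 5.4% |
| 20% v 20% | 2 | 6.4% | 6.0% |
| 17% v 23% | 1 | 7.5% | 5.6% |
| 15% v 25% | 0 | 5.0% | 5.3% |
| 15% v 25% | 1 | 9.8% | 6.8% |
| 15% v 25% | 2 | 15.0% | 6.0% |
| 10% v 30% | 0 | 5.2% | 5.8% |
| 10% v 30% | 1 | 21.8% | 5.8% |
| 10% v 30% | 2 | 43.5% | 4.9% |

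Further runs of 3,000 trials at *d* = 1 gave 9.8% and 10.1% for 15% v 25%, and 19.3% and 21.1% for 10% v 30%. The hand approximation agrees. With a regimen term the rate stays near nominal (4.9% to 6.8% in the table). The *d* = 0 rows stand for a baseline marker, which randomisation balances, and show no inflation.

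**Binary illustration (assumed inputs).** Undetectable HBV DNA at week 12 in 50% v 90%, loss in 10% v 30%, independent within each arm.

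- Undetectable: 25 + 45 = 70 patients, with 2.5 + 13.5 = 16 losses.
- Detectable: 25 + 5 = 30 patients, with 2.5 + 1.5 = 4 losses.
- Crude odds ratio: (16/54) / (4/26) = 1.93. The within-regimen odds ratio is 1.0.
- With loss 15% v 25%: (15/55) / (5/25) = 1.36.
- With loss equal at 20%: (14/56) / (6/24) = 1.0.

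**The case against.** **Equal response.** The protocol plans a single active rate and hopes for high HBsAg loss with both regimens. At equal loss there is no bias. A reader might take the aim of showing superiority of A and/or B over control as a sign that the two regimens are expected to differ. It is not: the phrase says which comparisons with control may succeed. This objection stands, and it makes the problem conditional. It does not remove it, since equality is neither established nor stated for the tenofovir arm, and the marker analysis need not depend on it.

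**Potency and HBsAg loss.** Section 1 reports that one year of nucleoside analogue did not raise HBsAg loss, and that adding lamivudine to Peg-IFN made no difference (12% either way). All patients enter with HBV DNA below 20,000 IU/mL and both arms receive Peg-IFN, so the early virological gap may be small. It is therefore too strong to say that early HBV DNA will differ by arm; the text supports only that it may.

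**Silence is not exclusion.** Covariates of a secondary model are often left to an SAP. That is fair for the multivariable step. It does not cover the screen, which the protocol itself fixes as univariate.

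**Genotype A.** Section 7.2 says "A stratification for hepatitis B genotype A will be performed", and a reader might infer that a genotype term is missing for the same reason. The mechanism does not carry over. Stratification balances genotype A across arms, so it cannot reveal the regimen, and a marker correlated with genotype can still be a useful predictor. Forcing both regimen and genotype would also use both places that the protocol's rule allows at 20 responders.

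**Conclusion.** The point holds for markers measured after randomisation, and only for those. Section 9.1 screens them on pooled arms in a model that leaves out the randomised regimen, while Section 1 gives a reason to expect that early virology may differ by regimen. If HBsAg loss differs as well, the 5% test has a false-positive rate of about 10% (15% v 25% loss) to about 20% (10% v 30%) at a 1 SD marker difference. It is lower for smaller differences: 7.5% at 17% v 23%.

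These sizes rest on assumed differences in loss and in the marker. The documents do not support reading this as a bias in all the predictor models, nor as one certain to occur. This is an inexpensive improvement to a secondary analysis and does not touch the primary comparison with control.

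**What to change.** Add to Section 9.1 that each logistic model containing a marker measured after the start of treatment, up to week 12, at the screening and the multivariable step, includes randomised regimen as a forced term or is stratified by regimen. The marker is then judged by its regimen-adjusted likelihood-ratio test. Models with baseline markers only can stay as they are.

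No new data are needed, and nothing material is lost if the regimens respond equally. The cost is one degree of freedom. At the planned 20% response the responders/10 rule allows about two predictors, so a forced regimen term leaves room for one marker. Section 9.1 should say that regimen counts against that limit, and should work the limit at 0.20 as well as 0.50. A screening model of one marker plus regimen fits within it.

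Genotype A need not be forced or added to objective 2.2b. At most it can serve as a sensitivity analysis if there are enough responders.

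### The bootstrap in section 9.1 repeats only the multivariate model, not the marker selection that precedes it, and so overstates the stability of chance markers

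*Protocol*

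**What the plan says.** Protocol section 9.1 sets out the search for predictive markers (secondary objective 2.2b) as a sequence.

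1. Screening: "Univariate logistic regression analyses will be performed to identify predictors of response to the combination therapy".
2. Entry to the model: "Significant predictors from the univariate analysis will be combined into a multivariate logistic regression analysis".
3. Pruning: "the number of significant predictors from univariate analysis to be included in the multivariate analysis will be restricted following multi colinearity diagnostics".
4. Bootstrap, only under a condition: "If the number of potential predictors remains too large however, a bootstrap procedure will be followed". It consists of "drawing 200 samples of the same size as the original (n=100) with replacement, each time repeating the multivariate logistic regression analysis".
5. Use of the output: "Descriptives of this bootstrap procedure will be reported to identify a stable predictor set".

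One error level covers every step: "The level of significance during all these analyses is set at 0.05". The size limit is one predictor per 10 responders or non-responders, whichever are fewer, illustrated as follows: "With 100 patients included, the maximum number of predictors in a multivariate analysis is five, assuming a response rate of 0.50".

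The multivariate regression is the only step named as repeated. Section 9.1 names the univariate analysis separately, and no other section adds it to the resampling. No inclusion frequency that would make a marker stable is given.

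**The concern.** A bootstrap check of a selected model should show how far the selection would change in another sample of patients. For that, the selection has to be redone in each resample. Here the markers are chosen once, by their p-values in these patients, and the 200 resamples then refit only the chosen ones. A marker that passed by chance carries its chance association into every resample and never has to compete again with the candidates that were dropped.

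At stake is secondary objective 2.2b. Section 2.2 lists about 20 named markers plus open-ended genomic and proteomic candidates, at baseline and during the first 12 weeks. Section 9.1 does limit the number of predictors and prune for collinearity, but the bootstrap is the only check of stability it describes. The check applies exactly when the predictor set already exceeds the plan's own limit.

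**Working it through.** **Inputs from the protocol (section 9.1).** n = 100 treated patients; 200 resamples; level 0.05 at each step; events rule min(responders, non-responders)/10; response rate 0.50 in the predictor example and 0.20 in the sample-size assumption.

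**Assumptions (not in the protocol).** 30 candidate markers (range 20 to 60), normally distributed, independent or correlated at 0.3; two-sided Wald tests; sizes of real effects as stated below.

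**Step 1. The plan's own figure.** 100 × 0.50 / 10 = 5 predictors, as printed. At the response rate used for the sample size, 100 × 0.20 / 10 = 2. The bootstrap is therefore needed once 3 or more markers remain.

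**Step 2. How often it is reached if every marker is noise.** The number passing is Binomial(30, 0.05):

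P(3 or more) = 1 − (0.2146 + 0.3389 + 0.2586) = 0.188, about 19%.

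With 20 markers it is about 8%, with 60 about 58%. At the printed limit of five, P(6 or more) is 0.3% with 30 markers and 8% with 60. With 2 real markers (shifts of 0.9 and 0.7 SD) among 30, simulation gives about 58% at the limit of two.

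**Step 3. Why a screened chance marker recurs.** A resample centres on the observed association, so approximately z* ~ N(z, 1), and

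P(|z*| > 1.96) = Φ(z − 1.96) + Φ(−z − 1.96).

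| Observed p | z | Significant again |
|---|---|---|
| 0.05 | 1.96 | 50% |
| 0.03 | 2.17 | 58% |
| 0.01 | 2.58 | 73% |
| average over chance markers with p < 0.05 | – | 64% |

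An unscreened noise marker gives P(|N(0, 2)| > 1.96) = 17% (variance 2). So centring on the observed data raises the figure somewhat for any marker, and conditioning on passing the screen raises it much further.

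**Step 4. The procedure as written against the full procedure repeated.** Mean share of bootstrap refits in which a screened marker is significant; n = 100, response rate 0.20, 30 markers, more than 2 passing.

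| Setting | As written | Screen repeated in each sample |
|---|---|---|
| Noise markers, all noise, independent | 0.56–0.61 | 0.40–0.43 |
| Noise markers, 2 real among 30, independent | 0.49–0.53 | 0.34–0.37 |
| Noise markers, 3 real among 30, independent | 0.51–0.52 | 0.35–0.36 |
| Noise markers, all noise, correlated at 0.3 | 0.20–0.25 | 0.14–0.18 |
| Noise markers, 3 real among 30, noise correlated at 0.3 | 0.31–0.35 | 0.20–0.22 |
| Real markers, 2 real among 30 | about 0.78 | about 0.65 |

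A separate run with correlation 0.3 gave about 0.18 as written. With all-noise independent markers, other counts (20 to 60) and response rates (0.20 or 0.50) gave 0.55–0.63 as written and 0.27–0.52 with the screen repeated.

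**Reading.** Leaving out the screen adds about 15 percentage points for noise markers in the independent settings with 30 markers. The rest remains when the screen is repeated.

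**The case against.** Several counter-arguments have weight.

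- **The bootstrap is not a test.** A reader might set the 50–60% against a nominal 5% and call it a tenfold error inflation. That does not follow. An inclusion frequency is not a type I error rate, and any ordinary bootstrap centres on the observed data. The fair comparison is between the procedure as written and the same procedure with selection repeated.
- **No cut-off is stated.** A reader might infer that the plan certifies chance markers as stable. The protocol gives no frequency at which a marker counts as stable, and a statistical analysis plan may do so. With two real markers among 30, the as-written output still separates the groups on average: about 78% for real markers against about 50% for noise. At a cut-off of 70%, about 18% of screened noise markers and 70% of screened real ones would pass.
- **The step is conditional.** At the printed limit of five predictors, 30 noise markers would almost never trigger it. This is weaker than it looks, because the limit is two at the response rate on which the trial is sized.
- **Markers are correlated.** Section 2.2 lists several liver enzymes, and HBsAg and HBV DNA in more than one place. Correlation of 0.3 would largely escape collinearity pruning and lowers the figure to about 20–35%. The direction of the effect remains.
- **Omitting the screen is not the main source.** This stands: much of the recurrence persists when the screen is repeated.

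None of this answers the core point, that selection is the step the check leaves out.

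**Conclusion.** The point holds in a limited form. As section 9.1 is worded, the bootstrap refits only markers already selected in the same patients, so it omits selection uncertainty and makes chance markers look more stable than they are. Under the stated assumptions, and given that more than 2 markers pass, the figure for screened noise markers is about 50–60% of refits instead of about 35–45%. With correlated markers both figures are lower. The number of candidates, their correlation and the real effects are assumptions that the protocol does not fix.

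The documents do not support the stronger reading that the plan declares noise markers valid, or that repeating the screen would cure the problem. The primary comparison of HBsAg loss does not use this step.

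**What to change.** Amend the bootstrap sentence in section 9.1 to say, in substance: in each of the 200 bootstrap samples the complete selection procedure is repeated, namely univariate screening of all candidate markers, the collinearity step and the multivariate model, and inclusion frequencies are reported for all candidates, including those not selected in the original data.

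Add that these frequencies are descriptive and do not confirm a marker, because repeating the selection reduces the optimism without removing it. A run of the same procedure with the response permuted among treated patients may be shown as a reference. It need not be a mandatory threshold, since familywise control is a debatable requirement for an exploratory objective.

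Cost: a wording change and more computing time, with no extra patients, visits or samples. Inclusion frequencies of real markers also fall, from about 0.78 to 0.65 in the simulated case, so fewer markers will look convincing.

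### The fallback bootstrap for the predictor analysis is fixed at 200 samples; at least 5,000 with a recorded seed would remove avoidable Monte Carlo noise at almost no cost (a free improvement, not an error)

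*Protocol*

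**What the plan says.** Protocol section 9.1 (Descriptive statistics) screens markers by univariate logistic regression, carries the significant ones into a multivariate model, and limits their number by a rule that the count "should not exceed the number of responders (or non-responders, whichever is the lowest) divided by 10". It illustrates the rule: "With 100 patients included, the maximum number of predictors in a multivariate analysis is five, assuming a response rate of 0.50".

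The bootstrap consists of "drawing 200 samples of the same size as the original (n=100) with replacement" and refitting the multivariate model in every sample. It is a fallback, reached only after the collinearity checks: "If the number of potential predictors remains too large however, a bootstrap procedure will be followed". Its output is described in one sentence: "Descriptives of this bootstrap procedure will be reported to identify a stable predictor set". For the testing level, "The level of significance during all these analyses is set at 0.05".

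No inclusion frequency, cut-off or in/out rule is given for calling a predictor stable. Predictive markers are a secondary objective (sections 2.2 and 7.1.2).

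**The concern.** A bootstrap inclusion frequency is itself an estimate, and its precision depends on the number of resamples. The protocol fixes that number at a low value and then uses the output to decide which markers count as stable. The resulting noise adds to the sampling error of the trial but differs from it in kind: it does not come from the patients, and it can be made as small as one likes.

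At stake is whether another analyst with the same data and code, but a different seed, would report the same predictors. The primary comparison of HBsAg loss is not touched.

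**Working it through.** **Inputs from section 9.1.** B = 200 resamples; n = 100 treated patients; testing level 0.05; predictor limit = min(responders, non-responders)/10; planned response 0.20 on treatment.

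**Inputs assumed, because the protocol gives none.** Stability is judged by the inclusion frequency f, with a cut between 50% and 80%. The number, strength and correlation of candidates are also assumed.

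**1. The plan's own figure, and whether the fallback would be reached.** 100 × 0.50 / 10 = 5, as stated. At the treated response used for the sample size ("is assumed to be 0.01 under the null hypothesis and 0.20 under the alternative hypothesis"), the same rule gives 100 × 0.20 / 10 = 2. Section 2.2 lists more than a dozen markers, at baseline and over the first 12 weeks, so the fallback could well be used.

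**2. Precision of one inclusion frequency.** SE = √(f(1−f)/B).

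| B | f = 0.5 | f = 0.6 | f = 0.7 | 95% half-width at f = 0.5 |
|---|---|---|---|---|
| 200 | 3.5 points | 3.5 | 3.2 | 6.9 |
| 1,000 | 1.6 | 1.5 | 1.4 | 3.1 |
| 5,000 | 0.7 | 0.7 | 0.6 | 1.4 |

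From 200 to 5,000 the SE falls by √25 = 5.

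**3. One marker, two seeds.** If q is the exact binomial chance that a run places the marker at or above the cut, two runs disagree with probability 2q(1−q). The ranges cover cuts of 50% to 80%.

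| True frequency above the cut by | B = 200 | B = 5,000 |
|---|---|---|
| 0 points | about 50% | about 50% |
| 3 points | 20-29% | below 0.1% |
| 5 points | 4-13% | below 0.1% |
| 7.5 points | 0.2-3% | below 0.1% |
| 10 points | 0.3% or less | below 0.1% |

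**4. Whole sets, simple model.** Suppose k independent candidates have true frequencies spread evenly over a range of width W that contains the cut. The average disagreement per marker is close to m = 1.128 × SE / W, and the sets differ with probability 1 − (1 − m)^k. For a 60% cut:
- W = 0.60 (30-90%), B = 200: m = 1.128 × 0.0346 / 0.60 = 0.065. Sets differ in 29%, 42% and 55% of pairs for k = 5, 8 and 12.
- Same W, B = 5,000: m = 0.013, giving 6%, 10% and 15%.
- W = 1.00 (0-100%), B = 200: m = 0.039, giving 18%, 27% and 38%.

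The answer depends strongly on the assumed spread, so the model shows sensitivity and is not a forecast.

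**5. Whole sets, actual logistic bootstraps at n = 100.** The full model was refitted in each sample, with inclusion at p < 0.05. Three sets of simulations with different assumed effects gave, for the chance that two seeds name different sets:

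| Simulation | B = 200 | B = 5,000 |
|---|---|---|
| 6-12 candidates, response 0.20 or 0.50, cuts 50-80%, 60 data sets per scenario | 4-27% | 0-6% |
| 6, 8 or 12 correlated candidates, half with moderate effects, cuts 50-70%, 15 data sets per scenario | 6-39% | 0-12% |
| Assumed effects, cuts 50-70% | about 8-23% | 0-4% |

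**6. Comparison with sampling error.** In the first simulation, with bootstrap noise almost removed (2,000 samples), two different data sets of 100 patients gave different predictor sets in 67-98% of pairs.

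**The case against.** The strongest reply is that the protocol promises descriptives and no automatic selection. Reported as descriptives, 58% in one run and 62% in another are the same finding; a flip needs a hard cut, which the reader has to supply and which a statistical analysis plan may define. The bootstrap is also conditional and serves a secondary objective. Two hundred samples separate clearly stable from clearly unstable markers: ten points from the cut, two runs disagree in 0.3% of pairs or fewer. Sampling error is far larger and is unaffected by B.

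Most of this stands. It rules out a stronger reading that a reader might infer, namely that two runs would often name different predictors and that the published set could not be reproduced. That needs many candidates crowded around an assumed cut. Disagreement above one half appears only in the simple model with 12 candidates confined to 30-90%; in the logistic simulations most pairs agree. The protocol makes no reproducibility claim that 200 samples would break.

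What does not stand is that dominant sampling error makes the choice of B immaterial. Sampling error cannot be removed once the data are in; seed error can. And the number 200 is written into the protocol, so it is not a detail left open.

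**Conclusion.** A free improvement, not an error. The standard error of up to 3.5 points (95% about ±7) on an inclusion frequency follows from B = 200 alone. The effect on the named set rests on assumptions: stability judged by inclusion frequency, a cut of 50-80%, and the candidate numbers and effects simulated. Under these, two seeds could give different sets in roughly 5-40% of cases at 200 samples and roughly 0-12% at 5,000. Only markers within a few points of the cut are exposed. A predictor set that survives 5,000 resamples is still fragile as a statement about future patients, because it comes from 100 patients.

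**What to change.** In section 9.1, replace 200 samples by at least 5,000 samples and state that the random seed is recorded. The seed alone would let the run be repeated exactly, but the result would still depend on which seed was chosen; the larger number reduces that dependence. The cost is one number and a short clause: 2,000 logistic fits at n=100 with eight predictors took about 0.2 seconds, so 5,000 would take about 0.2 × 5,000 / 2,000 = 0.5 seconds. Design, sample size and primary analysis are unchanged.
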